### Data monitoring

Data monitoring committee, interim analyses, or stopping guidelines are not included in this study because all the treatment approaches applied in this study are already in daily practice and the results have been acceptable. However, any unexpected adverse events that occurred during the intervention period will be reported to a highly experienced physiotherapist who will not be involved in the execution of the trial. This physiotherapist will be available to make the final decision to terminate the trials in case of unanticipated harm.

### Harms

No potential harm is anticipated for the participants of this study. All complications and harms (in case of any) will be reported to a highly experienced physiotherapist who will be available to make the final decision to terminate the trial participation for a participant in case of unanticipated harm. All the complications and harms (in case of any) will be reported also to the Research Ethics Committee. Major and minor complications (in case of any) will be listed in the safety consideration section.

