### Description of the interventions

#### Patient-led goal-setting approach

The intervention will be carried out for 8 weeks including 5 face-to-face sessions. The first session takes about 1 h, and the other sessions are held for 15 to 30 min with 2-week intervals. Then, two follow-up sessions (lasting 30 min each) will be developed with a 1-month interval; furthermore, one session will be organized 12 months after the first session, and finally, the results will be collected. The SMART model will be used for applying this intervention. This model includes a special process for goal setting that is measurable, achievable, and associated to a specific time return. In this model, the researcher is trained in setting goals by the patient, considers the patient’s history of LBP, and discusses about the issue that led to the occurrence of LBP [4]. Patients are asked to prioritize these problems based on what they want to focus on. Then, the strategies are discussed based on evidence-based guidelines, and the patient sets specific goals and strategies to work independently between sessions. Patients record their set goals, progress towards these goals, and agree on strategies for achieving the goal in their workbooks. If the goal strategies include consultation with a health care professional, the patient is encouraged to pursue this independently (Table 1) [3–5].

**Table 1 Tab1:** Components of the interventions

Patient-led goal-setting intervention
Session 1: week 1
► Orientation of patient
► SMART approach explained
► Goals and strategies developed
Homework task: review educational material
Session 2: week 3
► Education and discussion
► Review of goals, progress towards, and barriers to achieving goals
► Strategies developed
Sessions 3 and 4: weeks 5 and 7
► Review of goals, progress towards, and barriers to achieving goals
► Strategies developed
Session 5 (completion of the intervention): 2 months
► Review of goals, progress towards, and barriers to achieving goals
► Strategies developed
► Outcomes measured
Post-intervention follow-up (3 months)
► Review of goals, progress towards, and barriers to achieving goals
Post-intervention follow-up (4 months)
► Review of goals, progress towards, and barriers to achieving goals
► Outcomes measured
Post-intervention follow-up (12 months)
► Outcomes measured

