#### Pain neuroscience education

It includes 4 sessions being organized once a week for 40 to 45 min in person and in each session issues such as neuropathic pain, allodynia, central sensitization, hyperalgesia, peripheral nerve sensitization, neuroplasticity, spreading pain, stress biology, immune response, hypersensitivity, fear, tragedy and pain, and how to cope with pain will be discussed to patient through pictures, terms, and descriptions (Table 2) [12].

**Table 2 Tab2:** The content of neuroscience pain education

1 session	Peripheral neuropathic pain, peripheral nerve sensitization, allodynia, central sensitization, hyperalgesia
2 sessions	Neuroplasticity, spreading pain, central sensitization, hyperalgesia, allodynia
3 sessions	Stress biology, immune response, emotional overload, fear, catastrophization, pain
4 sessions	How to cope with pain?

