#### Manual therapy

MT includes 18 sessions of treatment for 6 weeks lasting 60 min each. Soft tissue mobilization, muscle energy techniques, and joint mobilization will be planned to be performed. Soft tissue mobilization includes myofascial stretching for superficial and deep muscles and transverse friction for intervertebral and supraspinal ligaments. Muscle energy techniques include relaxation after isometric contraction for the quadratus lumborum and piriformis muscles that we ask patients to gently contract for 8 s at 30% of maximum voluntary contraction force, and this movement will be repeated after each rest interval. Joint mobilization will be evaluated based on sacroiliac mobility test with standing flexion forward test, Gillet test, and Piedallu Sign test [7, 8].

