### Description of the control

Participants in the control group will receive no specific intervention. However, for meeting the ethical codes, we will provide the patients in the control group with a pamphlet included with useful information on taking care during chronic LBP.

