### Outcome measures

All the outcome measures explained below were recorded at baseline (pre-test), 2 months post-test, and 4 and 12 months follow-up time points. The flow of the study is also provided in Table 3.

**Table 3 Tab3:** Schedule of enrollment, intervention, study visits, and assessments for all three study groups

Time point	Study period													
	Enrollment	Allocation	Patient-led goal-setting group with PNE				Patient-led goal-setting group with MT				Control group			
			Start	2 m	4 m	12 m	Start	2 m	4 m	12 m	Start	2 m	4 m	12 m
Enrollment														
Eligibility screen	*													
Informed consent	*													
Baseline assessment	*													
Allocation		*												
Intervention														
Patient-led goal-setting group with manual therapy							*	*	*	*				
Patient-led goal-setting group with PNE			*	*	*	*								
Assessments														
Start back			*				*				*			
QBPDS			*	*	*	*	*	*	*	*	*	*	*	*
NRS			*	*	*	*	*	*	*	*	*	*	*	*
SF_36			*	*	*	*	*	*	*	*	*	*	*	*
DASS			*	*	*	*	*	*	*	*	*	*	*	*
PSEQ			*	*	*	*	*	*	*	*	*	*	*	*
FABQ			*	*	*	*	*	*	*	*	*	*	*	*
Tampa Scale			*	*	*	*	*	*	*	*	*	*	*	*
PCS			*	*	*	*	*	*	*	*	*	*	*	*
RNPQ			*	*	*	*	*	*	*	*	*	*	*	*
CSI			*	*	*	*	*	*	*	*	*	*	*	*
Adverse events			*	*	*	*	*	*	*	*	*	*	*	*

*PNE* pain neuroscience education, *MT* manual therapy, *NRS* Numerical Rating Scale, *QBPDS* Quebec Back Pain Disability Scale, *PSEQ* Pain Self-Efficacy Questionnaire, *DASS* Depression Anxiety Stress Scale, *FABQ* Fear Avoidance Beliefs Questionnaire, *TSK* Tampa Scale for Kinesiophobia, *PCS* Pain Catastrophizing Scale, *CSI* Central Sensitization Inventory

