### Plans to promote participant retention and complete follow-up

To ensure an adequate follow-up rate, the research team will:Maintain regular contact with participants after giving informed consent (regularly every 4 weeks)Ensure contact occurs in the 4 weeks prior to the baseline assessment (pre-test), to ensure greater levels of contact between consent and the intervention startingAfter randomization, participants will be given the opportunity to meet a specific therapist and ask questions prior to the intervention startingParticipants will be reimbursed for their transportation expenses

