### Improve adherence to the intervention protocols where an intervention appointment is missed

The research assistant will follow up non-attendees via telephone call to ascertain the reason for non-attendance and whether any assistance from the study team can help in this matter.The research assistant will check if the participant is still willing to continue with the appointed intervention and the study time points outcome measure assessments. In case a participant discontinued the intervention protocol for more than 3 sessions, they would not be included in the analysis.

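### Ending trial participation after unanticipated harm, rather than only the assigned treatment, may lose later outcome and safety assessments, and the more-than-3-sessions exclusion also removes participants stopped for harm

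*Protocol article*

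**What the plan says.** **Harms (protocol article).** No harm is anticipated. If harm occurs, an experienced physiotherapist is available to "make the final decision to terminate the trial participation for a participant in case of unanticipated harm". The same section sends all complications and harms to the Research Ethics Committee and has major and minor complications listed.

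**Adherence section (missed intervention appointments).** A research assistant telephones non-attendees and asks whether they will go on with the intervention and with the outcome assessments. The section then sets an exclusion: "In case a participant discontinued the intervention protocol for more than 3 sessions, they would not be included in the analysis". It makes no exception for stops due to harm.

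**Session numbers.** Goal setting, common to both active arms: "The intervention will be carried out for 8 weeks including 5 face-to-face sessions". PNE: "It includes 4 sessions being organized once a week". MT: "MT includes 18 sessions of treatment for 6 weeks lasting 60 min each". Control: "Participants in the control group will receive no specific intervention", apart from a pamphlet.

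**Assessments.** "All the outcome measures explained below were recorded at baseline (pre-test), 2 months post-test, and 4 and 12 months follow-up time points". Table 3 also schedules adverse events at each of these times in all three groups. The retention section adds contact every four weeks after consent. The Statistical analysis section assumes that missing data are missing at random.

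**The concern.** Stopping a treatment that may have caused harm and ending a person's participation in the trial are different decisions. The first protects the participant; the second can also end data collection. The Harms section gives the physiotherapist the second and does not limit it to the first.

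Safety follow-up is the main stake. A participant with an unexpected harm is one whose further course should be recorded, and the Data monitoring section provides no monitoring committee. The first report would exist, but recovery, persistence or further events at the scheduled visits might not be captured.

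Bias is the smaller stake. If participants removed for harm have worse pain or disability than those who stay, in a way their earlier data do not predict, missing at random is doubtful for them. If removals also differ by arm, the arm that loses more of them looks slightly better than it was. The exclusion after more than 3 discontinued sessions adds to this, since it drops harm stops from the analysis even when their outcomes have been collected.

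**Working it through.** The plan gives no figure on this point, so there is none to reproduce. The check has three parts.

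**1. Does any text keep a participant stopped for harm in follow-up?**
- Harms: ends trial participation; does not say what happens to assessments.
- Adherence section: names treatment and assessments separately, but only after a missed appointment and subject to the participant's willingness.
- Retention section: four-weekly contact, not tied to harm.
- Table 3: schedules outcomes and adverse events for every group, but does not address someone whose participation has ended.

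None of these provides for continued assessment after a harm stop.

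**2. How does the more-than-3-sessions rule treat harm stops?**

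The article does not say which sessions count, so both readings are shown. A participant is excluded if more than 3 sessions remain.

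*Counting only MT or only PNE sessions:*
- MT: a stop after session s leaves 18 − s. After session 14, 4 remain (excluded). After 15, 16 or 17, there remain 3, 2 or 1 (kept).
- PNE: a stop after session s leaves 4 − s. Before session 1, 4 remain (excluded). After 1, 2 or 3, there remain 3, 2 or 1 (kept).

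*Counting goal-setting sessions as well* (weeks 1, 3, 5, 7 and 2 months, from Table 1). Assumed: MT and PNE both start in week 1, and MT runs at 18/6 = 3 sessions a week.
- PNE, end of week 3: 1 + 3 = 4 remain (excluded). End of week 4: 0 + 3 = 3 remain (kept).
- MT, end of week 4: 6 + 3 = 9 remain (excluded). After session 16: 2 + 2 = 4 (excluded). After session 17: 1 + 2 = 3 (kept).

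So the same harm at the end of week 4 removes an MT participant from the analysis (9 left) and keeps a PNE participant (3 left). The control group has no sessions to discontinue. For MT stops up to session 14, the exclusion rule alone already determines the analysis. The Harms wording affects the analysis by itself only for late MT stops, PNE stops with 3 or fewer sessions left, removals during follow-up, and controls. The last two are less likely: the Data monitoring section refers to events in the intervention period, and controls receive only a pamphlet.

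**3. How large could the bias be?**

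Inputs: 105 patients (Eligibility criteria), taken as 105/3 = 35 per arm. Assumed, because no harm rate is given: k = 1 or 2 removed from one arm and none from the others, each d points worse than the full arm mean on the 0–10 pain scale in a way that earlier data do not predict. One is 1/35 = 2.9% of an arm and two are 2/35 = 5.7%, both within the 10% loss planned for in the Sample size estimation section.

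If the full arm mean is μ, the mean of those left is [35μ − k(μ + d)]/(35 − k) = μ − dk/(35 − k). The apparent improvement is dk/(35 − k):

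| d | k = 1 | k = 2 |
|---|---|---|
| 0 | 0 | 0 |
| 1 | 1/34 = 0.03 | 2/33 = 0.06 |
| 3 | 3/34 = 0.09 | 6/33 = 0.18 |

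**The case against.** The best defence is that the Harms section says who decides and does not say that assessments stop or that data are discarded. Follow-up after withdrawal is a detail that an article often leaves to the full protocol. The drafting is also loose: the Data monitoring section has what appears to be the same adviser terminating the trials, so the choice of words may be shorthand for stopping treatment. The adherence section shows that the authors do distinguish treatment from assessments. All this stands as a reason for caution. A reader might infer that follow-up will certainly end after a harm stop; the text supports only that it may. What remains is that the rule, as stated, is set at the wider level and nothing in the article narrows it.

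A reader might also infer that the harm itself would go unrecorded. That is not so: it is reported to the physiotherapist and the ethics committee and listed. Only the later scheduled assessments are at risk.

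Finally, a reader might infer that the Harms rule favours one arm. It contains nothing that depends on arm. The uneven effect comes from the 3-session threshold alone, and its exact form depends on start weeks and a counting rule that the article does not give.

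**Conclusion.** The point holds as a minor one. The Harms rule reaches further than protecting the participant requires and may cost later scheduled outcome and safety data. The exclusion rule separately removes harm stops from the analysis, more readily in the MT arm than in the PNE arm.

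The documents do not support a claim of material bias. No harm rate is given, none is anticipated, and both k and d above are assumptions. The largest figure, 0.18 points, needs two removals in one arm, none elsewhere, and each participant 3 points worse than the arm mean in a way their earlier scores do not predict. If the harm is unrelated to back pain, or removals are equal across arms, the bias is near zero. The case for change rests mainly on safety follow-up and on keeping participants in the arm to which they were randomised.

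**What to change.** - **Harms:** reword so that the physiotherapist's decision stops the assigned intervention only. State that the 2-, 4- and 12-month outcome and adverse-event assessments continue unless the participant withdraws consent.
- **Adherence section:** exempt participants stopped for harm from the more-than-3-sessions exclusion, and analyse them in their randomised arm.
- **Reporting:** give the number stopped for harm in each arm.

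When treatment should be stopped remains for the sponsor to decide. The cost is one or two sentences and one exemption. The visits are already scheduled, so the only burden is a little effort to keep in contact with the few participants affected.

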### Protocol amendments

In the case of modification of the study protocol, all changes will be updated to the Iranian Registry of Clinical Trials.

### Confidentiality

Trial data will be stored in a secure storage at the study center for 10 years after the completion of the study. All data will be handled based on the reasonable request from the corresponding author.

### Implementation

The recruitment is done by a researcher who is not involved in the execution of the treatment approaches and the outcome measure analysis. After receiving the written consent, this researcher opens the envelope, and the patient is then randomized to one of the study groups. A blinded assessor ([name]) carries out the baseline measures, and the patient receives a written guide for the treatment approach.

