### Allocation

Block randomization will be used in this study. A person not involved in the execution of the trial generates the randomization list using block randomization via computer-generated random numbers. The same person prepares sealed envelopes containing the treatment allocation information. The block size is not revealed to the study group before analyses. The envelopes are stored in a secure place at the study center. After receiving the informed consent, a researcher who did not apply the intervention (treatment approaches) or evaluate the outcomes gives a sealed envelope to the patient containing the treatment allocation information, and the treatment is arranged accordingly.

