### Blinding

The blind researcher will be blinded from the treatment allocation when collecting the outcome measurements. The patient will be wearing long-covered clothes during the follow-up visits and asked not to reveal the given treatment. The blinding of the treatment approach is not possible for the personnel executing the treatment approach nor the patients. This study will be conducted as a pre-test/post-test design with a control group and blinded assessor and data analyst.

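### The protocol contradicts itself on whether baseline questionnaires come before or after the allocation envelope is opened; if after, unblinded patients may rate their baseline knowing their arm

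*Protocol article*

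**What the plan says.** Protocol article, Implementation: once written consent is in hand, "this researcher opens the envelope, and the patient is then randomized to one of the study groups". The next sentence says that a blinded assessor "carries out the baseline measures, and the patient receives a written guide for the treatment approach".

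Protocol article, Allocation: after consent, a researcher "gives a sealed envelope to the patient containing the treatment allocation information". This section does not mention baseline measurement.

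Protocol article, Blinding: "The blinding of the treatment approach is not possible for the personnel executing the treatment approach nor the patients".

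Protocol article, Outcome measures: "All the outcome measures explained below were recorded at baseline (pre-test), 2 months post-test, and 4 and 12 months follow-up time points". The text does not place baseline relative to allocation. In Table 3, the row "Baseline assessment" is starred under Enrollment, beside screening and consent and ahead of Allocation. The ten outcome instruments (QBPDS, NRS, SF-36, DASS, PSEQ, FABQ, Tampa, PCS, RNPQ, CSI) have no star under Enrollment. Each is first starred under Start within an arm, to the right of Allocation.

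Protocol article, Statistical analysis: a mixed-model ANOVA with group and time as fixed factors compares pre-test with post-test within groups and compares groups at each time point. The main conclusion is unadjusted.

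**The concern.** Baseline should be fixed before anyone, the patient above all, can know the allocation. Both primary outcomes and all the secondary ones are questionnaires that the patient answers, so what counts is what the patient knows. A patient who has just learned that the arm is a pamphlet, or an active programme, may rate pain, disability, mood or self-efficacy differently from one who does not yet know.

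A baseline taken after allocation can itself be affected by allocation. Baseline is one of the four time levels in the planned model and the reference for every change from pre-test, so a difference produced in this way would enter the group-by-time contrasts. It cannot be removed afterwards unless someone knows which patients were measured in which order.

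**Working it through.** The protocol states no figure on this point, so the check sets the sections side by side and then traces where a shifted baseline would enter the analysis.

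**Order of steps**

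1. Implementation, read in sentence order: consent, envelope opened and patient randomized, baseline measures, written treatment guide. The order is implied by sequence; no word says that baseline comes before or after the envelope.
2. Allocation: consent, then the envelope goes to the patient. This supports only the first link and says nothing about baseline.
3. Table 3, baseline row: baseline before allocation.
4. Table 3, instrument rows: first measurement at Start, after allocation.
5. Eligibility criteria: an NRS and a QBPDS score are needed to enter, and Table 3 puts screening under Enrollment. A reading of both primary outcomes should therefore exist before allocation. No section says that these readings are the analysis baseline, and they cover none of the secondary questionnaires.

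Items 1 and 4 point one way and item 3 the other. Item 2 is neutral on baseline. Item 5 provides a pre-allocation value for two of the ten instruments.

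**Where a shift would enter**

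Let *T* be the true difference between two arms at follow-up, *a* the difference in reported baseline caused by knowing the arm, and *b* the corresponding reporting difference at follow-up.

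- Contrast in change, baseline taken before allocation: *T* + *b*
- Contrast in change, baseline taken after allocation: *T* + *b* − *a*
- Comparison at a follow-up time point alone: *T* + *b*

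The documents give neither *a* nor *b*. For scale only, assume that *a* lies between 0.25 and 1.0 NRS points in absolute size. The net distortion *b* − *a* is then, in absolute size:

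- *b* = 0 (effect gone by follow-up): 0.25 to 1.0 points
- *b* = *a*/2: 0.5 × 0.25 = 0.125 to 0.5 × 1.0 = 0.5 points
- *b* = *a* (effect fully persists): 0

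The sign is open. If disappointed controls rate baseline pain higher and this fades, control appears to improve and the benefit over control is understated. The opposite reaction would overstate it.

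**Which contrast**

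The Aims section makes PNE against MT primary, each combined with goal setting. Both arms are active, so *a* is plausibly smaller than against a pamphlet. It cannot be set to zero: the programmes differ visibly, with 4 sessions of 40 to 45 minutes against 18 sessions of 60 minutes.

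**The case against.** The strongest reply is that this is loose drafting. Implementation never says that baseline follows the envelope, and the Enrollment row of Table 3 says that it does not. The participant-retention section lists contact before the baseline assessment ahead of its item on what happens after randomization, which by the same sentence-order reading suggests baseline first. Table 3 sets out assessments in blocks by arm, so a baseline shown by arm has to sit under Start; even the STarT Back screening tool appears only there. A blinded assessor at baseline need not mean that allocation has happened, because the Discussion has one person doing pre-test, post-test and follow-up. Implementation also has the researcher open the envelope and mentions the patient's written guide only after the baseline measures, so the patient might not yet have been told.

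Much of this stands. A reader might infer that patients in this trial did report baseline knowing their arm, or that a bias of a particular size passes in full into the primary effect. The documents support neither. The order is disputed within the protocol. The size and sign of any shift are unknown, and a persisting effect would partly or wholly cancel in change scores. The planned between-group comparisons at follow-up time points do not use baseline at all.

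What the reply does not remove is the contradiction. The section describing how staff proceed and the instrument rows of the schedule both read as baseline after allocation, and the Allocation section hands the envelope to the patient directly after consent. The eligibility scores do not settle the matter, since they are not named as baseline.

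**Conclusion.** The point holds as a contradiction with a conditional bias risk. Implementation (by sentence order) and the Start columns of Table 3 place the baseline measures after the envelope; the baseline row of Table 3 places them before it. If the Implementation order was followed and patients learned their arm at that point, self-reported baseline scores became open to influence by allocation, and assessor blinding would not prevent it.

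No size can be given from the documents. The range in the working rests on an assumed shift and on an assumption about how much of it persists to follow-up. The risk bears mainly on contrasts with control and on analyses of change, less on PNE versus MT and not on comparisons at follow-up alone. It is more than missing detail, because two stated orders conflict and only one keeps baseline clear of allocation.

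**What to change.** State one order in Allocation, Implementation and Outcome measures: consent, eligibility, all baseline questionnaires completed, and only then the envelope opened. In Table 3, move the baseline stars for all ten outcome instruments from Start to Enrollment.

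For patients already enrolled, record from dated forms whether baseline preceded the envelope. This matters more than the rewording: the Trial status section gives a recruitment start of 22 October 2021 and expects completion in the first quarter of 2023, ahead of publication on 8 September 2023, so a new order may reach few patients. Where baseline came second, run a sensitivity analysis that either uses the eligibility NRS and QBPDS scores as baseline or compares groups at follow-up without the post-allocation baseline. The second option is the only one for the secondary outcomes. Simply excluding the affected patients is not advisable, since it could remove everyone if Implementation was followed literally.

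The cost is protocol wording, a date check and one sensitivity analysis. No further patients or measurements are needed.
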